## Abstract

**Background:**

Catheter-associated urinary tract infections (CAUTIs) are the main cause of health care–associated infections, and they increase the disease burden, antibiotic usage, and hospital stay. Inappropriate placement and unnecessarily prolonged usage of a catheter lead to an elevated and preventable risk of infection. The smartphone app Participatient has been developed to involve hospitalized patients in communication and decision-making related to catheter use and to control unnecessary (long-term) catheter use to prevent CAUTIs. Sustained behavioral changes for infection prevention can be promoted by empowering patients through Participatient.

**Objective:**

The primary aim of our multicenter prospective interrupted time-series analysis is to reduce inappropriate catheter usage by 15%. We will evaluate the efficacy of Participatient in this quality improvement study in clinical wards. Our secondary endpoints are to reduce CAUTIs and to increase patient satisfaction, involvement, and trust with health care services.

**Methods:**

We will conduct a multicenter interrupted time-series analysis—a strong study design when randomization is not feasible—consisting of a pre- and postintervention point-prevalence survey distributed among participating wards to investigate the efficacy of Participatient in reducing the inappropriate usage of catheters. After customizing Participatient to the wards’ requirements, it will be implemented with a catheter indication checklist among clinical wards in 4 large hospitals in the Netherlands. We will collect clinical data every 2 weeks for 6 months in the pre- and postintervention periods. Simultaneously, we will assess the impact of Participatient on patient satisfaction with health care services and providers and the patients’ perceived involvement in health care through questionnaires, and the barriers and facilitators of eHealth implementation through interviews with health care workers.

**Results:**

To reduce the inappropriate use of approximately 40% of catheters (currently in use) by 15%, we aim to collect 9-12 data points from 70-100 patients per survey date per hospital. Thereafter, we will conduct an interrupted time-series analysis and present the difference between the unadjusted and adjusted rate ratios with a corresponding 95% CI. Differences will be considered significant when *P*<.05.

**Conclusions:**

Our protocol may help reduce the inappropriate use of catheters and subsequent CAUTIs. By sharing reliable information and daily checklists with hospitalized patients via an app, we aim to provide them a tool to be involved in health care–related decision-making and to increase the quality of care.

**Trial Registration:**

Netherlands Trial Register NL7178; https://www.trialregister.nl/trial/7178

**International Registered Report Identifier (IRRID):**

DERR1-10.2196/28314

## Introduction

### Background

Catheter-associated urinary tract infections (CAUTIs) are the main cause of health care–associated infections and lead to a higher disease burden, increased antibiotic usage, and prolonged hospital stay. Inappropriate placement and unnecessary prolongation of the use of a catheter lead to an elevated and preventable risk of infection.

The smartphone app Participatient has been developed to involve patients in communication and decision-making related to catheter use with the aim to overcome unnecessary (long-term) catheter use and prevent CAUTIs. Participatient can potentially empower patients to bring about sustained behavioral changes and prevent infections.

### Previous Studies

Participatient was developed at Dutch Hacking Health Leiden 2016 as a prototype smartphone app to prevent CAUTIs by involving patients in health care–related decision-making. The jury awarded the Participatient development team with the first prize nationwide for developing a patient involvement interface with an innovative design for infection prevention.

Participatient engages patients by providing them with personalized information regarding the appropriateness of their catheter, along with other medical and admission-related information.

The prototype was further developed in collaboration with patients, hospital staff, social scientists, engineers, eHealth experts, infection control professionals, and clinical microbiologists. We invited patients and staff in clinical wards to express their needs and concerns and to test, rate, and provide feedback on the initial versions of Participatient and its content.

Through 3 rounds of improvements, based on 5-10 interviews with patients [1], and 2-4 nurses per round, we developed the final version of the app. The interviews were based on the technology acceptance model [2] based on the usefulness and the ease of use of the app and its features. Furthermore, we majorly focused on patients’ skills in using technology and their eHealth literacy in order to increase the usability further [3,4]. The app was adjusted to the patients’ requirements by including additional information, although this was optional so as to not cause inconvenience to those with eHealth experience.

This led us to (1) generate iconic graphics to clarify text, (2) use visual feedback intermezzos containing motivational text or an explanation of the results, (3) use plain language adjusted to the level of understanding of patients in general, (4) develop clickable and thus optional instructions in the questionnaire, and (5) disseminate practical information, which was most valued by patients in the hospital wards. The patient information leaflet was digitized in the app.

After the development phase, a proof-of-concept study was conducted at a clinical ward at Leiden University Medical Center (LUMC), in which the technical and interactive aspects of the app were tested. All patients admitted to this ward were invited to download the app for use during their hospital stay. The app was introduced to the patients by the nurse who managed patient admission. We actively supported app use and assessed and adjusted the app through feedback options and a questionnaire. Users expressed positive opinions about the app’s purpose and design. We received some valuable feedback regarding the app’s content, which was generated using the Catheter Check content module. Users scored the app with 5 out of 5 stars.

### Participatient Content

During initial app use or “on-boarding,” the patient is asked to provide information regarding their ward of admission, gender, age group, and previous internet or app usage. This information is used to provide directed information regarding their admission. The app can be downloaded from the Apple App store and Google Play store on a patient’s smartphone or tablet device and comprises four content modules: Catheter Check, Admission Information, Pain Score, and Feedback. Finally, a Settings menu is included in the app (Figure 1).

Catheter Check is the catheter module, in which the appropriateness of catheter use is assessed by answering 8 questions. This yields a score in accordance with nationwide and worldwide criteria [5,6]. The result is displayed with personalized suggestions, promoting shared decision-making by motivating the patient to initiate dialogue with medical or nursing staff on the appropriateness of the presence of the catheter. Through daily reminders, patients are motivated to regularly check the indication of their catheter.

The Admission Information module comprises general medical information regarding infections, catheters, and the prevention of health care–associated infections for patients, but also practical information regarding the ward. From the patient feedback in the development phase, we learned that practical details including the visiting hours and telephone numbers of the ward were the most highly desired information. Participatient includes an information module with ward-specific information. In the proof-of-concept study, we used the patient information available in the ward’s paper-based records and digitized it in the app to include images and links.

The Pain Score module yielded an adopted pain score that accounts for various factors including mobility, medication, and myths and facts on pain relief. This module motivated patients to ask for adequate pain medication and medication to combat side effects including nausea when needed. Pain score evaluation is not a part of this study proposal. Nonetheless, this module has been developed for better pain registration, advice and education on side effects, and motivation of patients to seek better pain management, leading to an enhanced health care experience. Through daily reminders, patients are motivated to regularly score their need for pain medication.

The Feedback module contains an 8-question survey on patient satisfaction with the app and a link for email communication with the researchers.

In the Settings module, the daily reminders can be adjusted or turned off, and basic demographic characteristics, including gender, age group, and specialty and ward of admission, can be visualized and modified.

Participatient is available free of cost to all patients in the participating hospitals. The costs of adjustment and deployment are covered by the research team. App download and usage are limited by a code that is provided to the patients on admission.

Through the Admission Information and Pain Score modules in the app, users can avail of information and advice on other useful topics in addition to the catheter. In the development and proof-of-concept phases, users appreciated the additional functions of the app and indicated that this further motivated them to continue using the app throughout their hospital stay.

**Figure 1 figure1:**
[figure not shown]
The Participatient app content.

## Methods

### Overview

The app will be introduced in various clinical wards at 4 hospitals participating in the study. The app will be adjusted in accordance with the requirements of each medical center. Through a stepwise approach, we will launch the study at multiple locations.

The study will be implemented at clinical wards with a training session for the nurses in each ward, which will include a “kick-off” day that involves a demonstration of the app and an interactive session with the research team. We will provide information and instructions for downloading and installing the app on leaflets, which are normally provided to patients upon admission. Posters and flyers with infographics elucidating the risk of nosocomial infections and the study are provided to the participating clinical wards.

In each ward, we shall assess the willingness among and potential barriers to patients and health care workers. Before launching the app at each ward, it will be adjusted and extended to contain local information, protocols, and links to relevant websites of the 4 participating hospitals.

At each ward, an ambassador, with an affinity for the study, is recruited from among the nursing staff to provide peer support. This has been tested and found to be very useful in the proof-of-concept phase of this study. For active engagement of the ward staff, we included a regular support day in the ward for technical and medical troubleshooting during the implementation phase and the postintervention phase.

This is an interrupted time-series (ITS) analysis with the implementation phase between the pre- and postintervention survey. After the implementation phase, we will record feedback from the wards with regard to the prevalence and indication of catheters during the previous surveillance period. This “mirroring” technique is used in intervention studies and patient care to motivate subjects to facilitate further improvements. This would foster awareness and help reduce the use of catheters. Integration of an app in the health care routine is a complex intervention, with the implementation process itself also adding to the intervention. We will use the Trials of Intervention Principles Framework [7] to evaluate the overall effect of app implementation. During the postintervention surveys, we will report data on app use per department. After the postintervention surveys, we will report the surveillance data per department and study site.

The Participatient website [8] contains general information regarding the study. For the implementation phase, the website will be revised and updated. After consulting patients and wards, we aim to provide relevant information from hospital admission to nosocomial infections. The relevant information provided in the app will be made available on the website.

### Participating Hospitals

The following hospitals participated in this study: clinical wards of the LUMC (Leiden, the Netherlands), with the introduction of the app as main intervention; clinical wards of the Haaglanden Medical Center (The Hague, The Netherlands)—a regional general hospital—with the introduction of the app as the main intervention; clinical wards of the department of internal medicine and neighboring specialties of the Amsterdam University Medical Center (Amsterdam, The Netherlands) and the Spaarne Gasthuis (Haarlem, The Netherlands) as the second hospital from the Reduce the Inappropriate Use of Urinary and Intravenous Catheters study, with the app as an addition to the intervention bundle.

### Patient Recruitment

All patients in the participating wards, aged ≥18 years, or their family members will be able to download the app from the Apple App store and Google Play store and use it on their personal smartphone or tablet device (Android, iPhone, or iPad devices). The patients and staff are included in each step of the process in accordance with the Patients Included charters on patient information resources.

#### Ethics Statement

All data are processed anonymously. The studies are and will be conducted in accordance with the tenets of the Declaration of Helsinki, and all procedures involving patients have been approved by the Medical Ethical and Institutional Review Board of the LUMC. Before conducting the interviews, distributing the questionnaires, or using the app, informed consent will be obtained, either in the verbal or written format in the case of interviews and paper-based questionnaires or in the digital format in the app before initial use, from all users to anonymize the data for analysis.

For clinical data on the improvement of care quality, consent will be obtained as described previously [6]. Patients are offered the option to opt out of the study at any time by being discharged by the treating physician, as stated in the hospital admission information [9].

#### Study Design

We will conduct a multicenter ITS consisting of a pre- and postintervention point-prevalence survey distributed among the participating wards to investigate the efficacy of the app in reducing the inappropriate use of catheters (Figure 2) [10].

**Figure 2 figure2:**
[figure not shown]
Interrupted time-series analysis design with point-prevalence surveys (PPS).

We will conduct the ITS as described previously [11]. Clinical data will be collected every 2 weeks for 6 months in the pre- and postintervention periods.

All admitted patients in the participating wards will be included in the point-prevalence survey regardless of app use, catheter presence, or urinary tract infection (UTI). A local study code will be generated for each patient for those with a catheter or a UTI. This code is a pseudonym to verify the collected data and rectify as required. This code will remain in the local hospital and only be used during the study.

During the point-prevalence surveys, the following data will be collected: demographic factors including gender, department and specialty of admission, age in decennia, and the date of admission; catheter use including the date of insertion of the catheter, indication of the catheter on insertion, and the indication of the catheter at the time of the survey; and UTI episodes occurring at the time of the survey and if a catheter was associated with them.

The presence and indications for catheter use will be extracted from the (electronic) medical records, nurses’ lists, and observations of the admitted patients. On the day of measurement, the indication of the catheter and the necessary patient variables will be collected.

#### Measurement of Patient Satisfaction

To investigate the secondary outcomes, namely the impact of the app on patient satisfaction with health care services and providers and the patients’ perceived involvement in health care, the following validated instruments will be included in the questionnaires. Paper-based questionnaires on satisfaction with care, trust in the physician, and communication will be distributed. These data will be collected along with additional data including gender, department and specialty, and age group. The questionnaire on patient satisfaction with the app will be administered through the app itself.

Satisfaction with care will be measured using the items of the Quality of Care Through the Patient’s Eyes (QUOTE) questionnaire [12]. In total, 6 items will be used to measure patient satisfaction with the physician and nurse.

Trust in the physician will be measured using Trust in physicians_short form (TRIP_sf), which is based on the Cologne Patient Questionnaire scale to evaluate the patients’ trust in physicians, which measures different aspects of trust during physician-patient interactions [13].

Self-efficacy during patient–health care provider communication will be measured with the 5-item version of the Perceived Efficacy in Patient-Physician Interactions (PEPPI-5) questionnaire, which assesses the subjective sense of patients’ confidence when interacting with their physicians and patient involvement in health care [14,15].

To assess patient satisfaction with the app, a short 8-item evaluation questionnaire on the ease of use, time investment, usefulness, and perceived effect of the app will be used. Patient feedback will be requested through leaflets, and there will be a dedicated button on the home screen in the app.

Moreover, sociodemographic factors and general previous usage of eHealth or apps among patients will be measured [3,4] to determine the presence of patient features that predict the use and satisfaction with the app. To determine whether the app is fit for use by a wide range of users, user information will be requested upon on-boarding (initial use).

We will evaluate the health care workers’ experience with the implementation of shared eHealth-related decision-making on the wards before and after comparison interviews to detect barriers and facilitators [16] in the wards at each center.

#### Analytical Data on App Use

Data on app usage and data obtained from the end users will be collected via the app and accompanying questionnaires. Usage data (analytics) on the number of downloads, the page views, and continued app usage will be collected. These data are traced to the users per ward, gender, internet or app experience, and age group, although they are not traceable to an individual level (privacy by design). User-provided data comprise the responses to the catheter check, pain score, and the use of the Admission Information module.

**Figure 3 figure3:**
[figure not shown]
Data collection and secure storage at the LUMC on ADAS and ProMISe servers. CAUTI: catheter-associated urinary tract infection, AUMC: Amsterdam University Medical Center; HMC: Haaglanden Medical Center; LUMC: Leiden University Medical Center; SG: Spaarne Gasthuis.

### Analysis

#### Sample Size

The sample size is based on our objective of reducing inappropriate catheter use by 15%, with a power of 80% and a Cronbach *α* of .05. We extracted data on the incidence of inappropriate catheter use from previous studies in similar health care systems, which was approximately 40% for catheters [17,18]. We aim to collect 9-12 data points from among 100 patients per survey date per hospital [19,20]. On designating a particular day to obtain measurements every 14 days at each center, a 5-month period before and after the measurements is required. We intend to carry out surveys for 6 months and to collect 12 data points. At the LUMC, the prevalence of catheter use is approximately 30% among hospitalized patients, based on our pilot survey. Thus, 1200 patients are required per period, of whom catheters were used for 400 patients, and catheter usage being inappropriate among 160 patients. On correlating for 10%-15% of the missing data, the sample size is set to 1320-1380 patients in the pre- and postintervention groups. We intend to include this number of patients at each hospital to analyze the effect of the interventions at each medical center.

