#### Statistical Analysis

We will conduct an ITS analysis, similar to the one performed previously [21,22]. ITS is considered a strong study design when randomization is not possible and can thus be used to investigate causal effects with an observational “natural experiment” approach. The Cochrane collaboration guidelines for ITS analyses will be used with an autoregressive integrated moving average model [23]. Because such a model relies on linearity, we will assess the stationarity of the mean and variance with time through differencing [24,25]. The primary analysis involves a comparison of inappropriate catheter usage before and after Participatient implementation. Because other changes in catheter usage could affect our outcomes over time, we will adjust the data for potential confounders, autocorrelation, and the underlying secular trend. Subgroup analyses will be performed on the basis of risk factors for catheters and UTIs, including the ward of admission, age group, internet or app use, and gender. Analyses will be conducted using SPSS (version 24, IBM Corp).

We will use figures to visualize trends and the impact of the intervention. We will present the difference in unadjusted and adjusted rate ratios with a 95% CI. Differences will be considered significant when *P*<.05. All analyses, including subgroup analyses, will be predefined in an analysis plan before their performance.

For questionnaire assessment, we will use descriptive statistics and compare patient satisfaction with health care, their involvement in care, and their trust in physicians, before and after implementing the app. Data on patient satisfaction regarding the usefulness and ease of use of Participatient will be analyzed using descriptive statistics and will be used for subsequent rounds of app improvement after the study.

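### The stated 80% power per hospital for a 15% reduction follows from the stated size under neither reading of 15%: a simple comparison gives 42% (relative) or 99.5% (percentage points)

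*Protocol article*

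**What the plan says.** The Sample Size section ties the number to a power target: "The sample size is based on our objective of reducing inappropriate catheter use by 15%, with a power of 80" per cent, with an alpha of .05 that it calls a Cronbach α. The baseline share of inappropriate catheters is taken from earlier studies, "which was approximately 40% for catheters". The plan is 12 two-weekly surveys per period with 100 patients each at every hospital, and the section concludes: "Thus, 1200 patients are required per period, of whom catheters were used for 400 patients, and catheter usage being inappropriate among 160 patients". An allowance for missing data raises 1200 to 1320-1380. The section then applies this number to each hospital, so that the effect can be analysed centre by centre.

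The abstract repeats the target in the same open form: "To reduce the inappropriate use of approximately 40% of catheters (currently in use) by 15" per cent. The Statistical Analysis section plans an interrupted time series with an autoregressive integrated moving average (ARIMA) model and states that "we will adjust the data for potential confounders, autocorrelation, and the underlying secular trend".

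**The concern.** A 15% reduction from 40% can mean 34% or 25%. The Objective, the Study Objective, the Sample Size section and both Results paragraphs leave this open, so a reader cannot tell which result would meet the primary objective. The required sizes under the two readings differ by a factor of more than six (1,016 against 152 catheters per period), and the stated 400 lies between them.

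The power claim is explicit, numeric and made for each hospital. If 15% is relative, a single hospital would more often miss a true effect of that size than detect it, and a non-significant hospital result would carry little information. If 15% is in percentage points, the simple comparison has far more power than stated, but that comparison is not the trend-adjusted analysis the plan describes.

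**Working it through.** **Inputs from the protocol article.** Baseline p1 = 0.40; target p2 = 0.34 (relative) or 0.25 (percentage points); alpha .05; power 80%; 400 catheters per period per hospital; 12 surveys per period; equal periods. Two-sided testing is my assumption, since the article says only "Differences will be considered significant when *P*<.05".

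**The plan's own figures.** 12 × 100 = 1200 patients. 400/1200 = 33.3%, whereas the pilot prevalence at the LUMC is about 30%, and 0.30 × 1200 = 360. 0.40 × 400 = 160. The number 1200 is therefore the survey schedule multiplied out. The 80% enters none of these steps.

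**Size needed, simple two-proportion test.** With p̄ = (p1 + p2)/2,

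n = [1.960·√(2p̄(1−p̄)) + 0.842·√(p1(1−p1) + p2(1−p2))]² / (p1−p2)²

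- 40% to 34%: (1.960 × 0.6828 + 0.842 × 0.6815)² / 0.06² = 1,016 catheters per period.
- 40% to 25%: (1.960 × 0.6624 + 0.842 × 0.6538)² / 0.15² = 152 catheters per period.

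The stated 400 is about 2.5 times too small for the first (1,016/400) and about 2.6 times too large for the second (400/152).

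**Power at the stated size.** z = [|p1−p2|·√n − 1.960·√(2p̄(1−p̄))] / √(p1(1−p1) + p2(1−p2)), and power = Φ(z).

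| Catheters per period | 40% to 34% | 40% to 25% |
|---|---|---|
| 400 (as stated) | z = −0.203, 42.0% | z = 2.603, 99.5% |
| 360 (30% of 1200) | z = −0.293, 38.5% | z = 2.367, 99.1% |

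**Attempts to recover 80%.** One-sided testing at 400 gives 54.5% and 99.8%. Across one- and two-sided tests, with and without continuity correction, the required number is 800 to 1,049 (relative) or 120 to 165 (points), never near 400. Treating all 1200 patients as if they had catheters gives 86.1% for the relative reading. At 400 catheters, 80% power corresponds to 40% falling to about 30.5%, that is 9.5 points or 24% relative.

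**Trend adjustment, illustration only.** Take a segmented model with a linear trend, 12 + 12 equally spaced points, no gap, independent binomial errors and a normal test of the step. The squared correlation between time and the pre/post indicator is 0.751, so the variance of the step is multiplied by 1/(1 − 0.751) ≈ 4.02 (4.04 with a slope change as well). The 400 catheters then carry the information of about 100, and power per hospital is about 14% (relative) or 62% (points). Other choices under this type of model:

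- t test: 13% and 58%
- autocorrelation of 0.2: about 12% and 53%
- a gap of 6 survey intervals for implementation: about 8.5% and 32%

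**Four hospitals pooled.** 4 × 360 = 1,440 catheters per period, assuming the LUMC prevalence and one common effect at all four.

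| Analysis | 40% to 34% | 40% to 25% |
|---|---|---|
| Simple comparison | 92% | over 99% |
| Same illustrative trend model | about 38% | about 99% |

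**The case against.** The article shows no power formula. It refers to cited sources for the 9-12 data points, which were not available here, so an undescribed simulation or time-series rule may lie behind the number. A reader might infer that a plain two-proportion sum was done and done wrongly. The text does not support that: no such sum is shown, and none of the versions tried gives 400. What stands is that nothing shown leads from 80% power to 1200 patients.

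The trend-adjusted figures are also open to challenge. The article names an ARIMA model with differencing, does not say which coefficient is tested, and defers the details to an analysis plan. A reader might take 14% and 62% as the power of this trial. They are not: they depend on the model chosen above, and only the direction, that adjusting for trend costs power, carries over.

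A reader might further conclude that the whole study is underpowered. That does not follow either. Pooled over four hospitals, the percentage-point reading keeps about 99% power even in the illustrative trend model. The Sample Size section, however, rests its claim on each hospital and not on pooling.

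Nor should ward clustering be added as a certain further loss. The same participating wards are surveyed before and after, so stable differences between wards largely cancel. Only variation within wards over time would matter, and the article gives no figure for it.

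Finally, the plan to report rate ratios with 95% confidence intervals gives some protection against reading a non-significant result as no effect. That softens the consequence but does not repair the power statement.

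**Conclusion.** The point holds. The 80% power stated for each hospital is not reproduced under either reading of 15%: it is 42.0% for 40% to 34% and 99.5% for 40% to 25%. These two figures need only the article's inputs and a two-sided test. With 360 catheters, which the article's own 30% prevalence gives, they are 38.5% and 99.1%. The undefined 15% is a fault in its own right, because it leaves the primary objective without a fixed target. Trend adjustment makes the per-hospital position worse under both readings, by an amount that cannot be fixed from this document. Whether the pooled study is adequate depends on the reading: it is under percentage points, and under the relative reading it is for the simple comparison only.

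**What to change.** In the Sample Size section, the abstract and the objectives:

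1. State the target as two explicit proportions, either 40% to 34% or 40% to 25%.
2. Replace the per-hospital 80% claim with the power, or the detectable difference, that the planned number of catheters delivers. Recompute it for the trend-adjusted effect, stating the model, the number and spacing of points, the autocorrelation and any implementation gap. Use one catheter count, since 400 and 30% of 1200 disagree.
3. Give the pooled four-hospital power beside it, with the assumption of a common effect stated.
4. Describe hospital-level results as estimates with 95% confidence intervals.
5. Replace Cronbach α, which is a reliability coefficient, with a two-sided type I error of .05.

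The cost is rewording and one recalculation, with no extra patients. The stated power becomes less favourable under the relative reading. Making the pooled estimate the powered primary analysis would be a design decision for the investigators, and by itself it would not restore 80% under that reading: the illustrative trend model still gives about 38%.

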## Results

Based on our objective of reducing the inappropriate use of approximately 40% of catheters by 15%, we aim to collect 9-12 data points from among 70-100 patients per survey date per hospital. We will conduct an ITS analysis, which is considered a strong study design when randomization is not feasible. We will present the difference in unadjusted and adjusted rate ratios with a 95% CI. Differences will be considered significant when *P*<.05.

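### The sample-size figures do not agree: 12 surveys of 100 patients give 1,200 per hospital and period, not 1,320-1,380, and 30% of 1,200 is about 360 catheters, not 400

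*Protocol article*

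**What the plan says.** The Sample Size section gives the survey effort as a range: "We aim to collect 9-12 data points from among 100 patients per survey date per hospital". It then settles on the top of the range for the number of surveys: "We intend to carry out surveys for 6 months and to collect 12 data points". The Study Design section agrees on the schedule: "Clinical data will be collected every 2 weeks for 6 months in the pre- and postintervention periods".

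For the catheter count, the section says "At the LUMC, the prevalence of catheter use is approximately 30% among hospitalized patients", citing a pilot survey, and takes about 40% of catheters to be inappropriate. From these it derives 1,200 patients required per period, 400 with a catheter and 160 with an inappropriate one. After an allowance of 10-15% for missing data, "the sample size is set to 1320-1380 patients in the pre- and postintervention groups". This number is meant to be reached at each hospital, so that the effect can be analysed by centre.

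Two other places give a different number of patients per date. The Results paragraph of the Abstract says "we aim to collect 9-12 data points from 70-100 patients per survey date per hospital", and the Results section says "we aim to collect 9-12 data points from among 70-100 patients per survey date per hospital".

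**The concern.** Three sets of numbers describe the same quantity and do not fit together.

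- **Survey scheme against target.** The 1,200 patients required are exactly what 12 surveys of 100 deliver. The allowance raises the target by 120-180 patients, but neither the number of surveys nor the number of patients per date is raised to supply them.
- **Patients per date.** It is 100 in one section and 70-100 in two others.
- **Catheters.** The 400 catheters attached to 1,200 patients do not follow from a prevalence of 30%.

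Inappropriate use is a proportion of catheters, so the catheter count is the denominator of the primary outcome. A centre planning its wards from the article cannot tell whether to provide for 70, 100 or 115 patients per survey date, or what denominator to expect.

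**Working it through.** **Inputs, all from the protocol article.** Surveys per period: 9-12, with 12 intended (Sample Size). Patients per date per hospital: 100 (Sample Size) or 70-100 (Abstract, Results). Catheter prevalence: about 30%. Inappropriate share: about 40% of catheters. Missing data: 10-15%. Stated results: 1,200 patients, 400 catheters, 160 inappropriate, and 1,320-1,380 after the allowance.

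**1. Reproducing the stated total.** 12 × 100 = 1,200. Then 1,200 × 1.10 = 1,320 and 1,200 × 1.15 = 1,380. The stated range is reproduced exactly, so it was obtained by multiplying the scheme's yield by 1.10-1.15.

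**2. Yield of the survey scheme, per hospital and period.**

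| Surveys | 70 per date | 100 per date |
|---|---|---|
| 9 | 630 | 900 |
| 12 (intended) | 840 | 1,200 |

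No stated combination reaches 1,320. At 12 surveys the target needs 1,320/12 = 110 to 1,380/12 = 115 patients per date. At 100 per date it needs 13.2-13.8 surveys; a thirteenth survey would give 1,300. Pooling hospitals does not help, because the target applies to each one.

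**3. Catheter count.** 0.30 × 1,200 = 360, and 0.40 × 360 = 144. The stated 400 is 40 (11%) above 360. The stated 160 is 0.40 × 400, so it carries the same discrepancy. Reaching 400 needs 400/0.30 = 1,333 patients, or a prevalence of 400/1,200 = 33.3%.

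**4. Catheters left after missing data, if 1,200 are surveyed.** 1,200 × 0.85 × 0.30 = 306 and 1,200 × 0.90 × 0.30 = 324.

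**5. Inflation convention.** To keep 1,200 evaluable one would divide: 1,200/0.90 = 1,334 and 1,200/0.85 = 1,412. The stated totals leave 1,320 × 0.90 = 1,188 and 1,380 × 0.85 = 1,173, which is 1.0-2.3% below 1,200.

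**6. Does the discrepancy matter for power?** The article does not say whether the 15% reduction is absolute (40% to 25%) or relative (40% to 34%, since 40% × 0.85 = 34%). Simple two-proportion power, two-sided 0.05 (an assumption, as sidedness is not stated), equal catheter numbers per period, ignoring the time-series structure:

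| Catheters per period | 40% to 25% | 40% to 34% |
|---|---|---|
| 400 (stated) | >99% | 42% |
| 360 (30% of 1,200) | 99% | 38% |
| 306 (after 15% missing) | 98% | 34% |
| 252 (12 × 70 × 0.30) | 95% | 29% |
| 189 (9 × 70 × 0.30) | 88% | 23% |

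By the same formula, 80% power needs 152 catheters per period for the absolute reading and 1,016 for the relative one. None of the counts above moves either reading across 80%.

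**The case against.** The strongest reply is that 100 per date is an aim and not a ceiling. The Study Design section includes every admitted patient on the participating wards, so the yield depends on how full the wards are. If 100 means usable records, surveying 110-115 per date for 12 dates gives exactly 1,320-1,380. That is a coherent reading, and it defeats the stronger inference, which a reader might draw, that the study can never reach its target. It does not remove the inconsistency: the article nowhere says that 100 means usable records, and a range of 70-100 sits badly with 110-115.

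A reader might also take 630 patients and 189 catheters as the plan's expected low end. That stacks two lower bounds, and the Sample Size section states that 12 surveys are intended. With 12 surveys the low end is 840 patients and 252 catheters.

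On the catheter count, the prevalence is only approximate. Moreover, 30% of 1,320-1,380 is 396-414, so 400 may belong to the inflated total and simply be attached to the wrong number. That may explain the figure, but the text still attaches 400 to 1,200.

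Finally, one might infer that an overstated catheter count undermines the 80% power. The calculation does not support this: the answer turns on whether 15% is absolute or relative, not on 400 against 360 or 306. In an interrupted time series, the number of time points and the autocorrelation also matter.

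**Conclusion.** The point holds as an internal inconsistency in the stated sample-size figures. The intended scheme at its stated aim gives 1,200 patients per hospital and period, 120-180 short of the stated size. Two sections allow as few as 70 per date, or 840 over the intended 12 surveys. The catheter count is 40 above, and the inappropriate count 16 above, what 1,200 patients give at the stated 30% and 40%.

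This rests on reading 100 as patients surveyed per date and on taking the 30% at face value. If 100 means usable records, the total fits but the article must say so and drop the conflicting 70-100. The inflation convention is a minor matter of 1-2% in evaluable patients. The severity is below must-fix: the figures should be corrected, but the correction by itself does not change whether the study is adequately powered.

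**What to change.** Use one set of figures in the Abstract, the Sample Size section and the Results section. Either of two routes resolves the conflict:

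- **Restate the yield.** Give 1,200 patient-surveys per hospital and period, about 360 catheters and about 144 inappropriate, with 306-324 evaluable catheters after 10-15% missing, and restate the power at that yield. Patient-surveys is the safer unit, because all admitted patients are surveyed every two weeks and a long-stay patient can be counted more than once.
- **Keep 1,320-1,380.** State that 110-115 patients per survey date are needed at each hospital over 12 surveys, and attach the catheter count to the total it comes from.

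On either route, give the same number of patients per date everywhere. If 70 patients or 9 surveys is kept as a lower bound, state the power there. If the allowance is meant to preserve 1,200 evaluable patients in full, divide by 0.90-0.85, which gives 1,334-1,412 (about 111-118 per date).

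The cost is a text correction in three places and a restated power. The first route makes the stated yield less favourable; the second may require more beds or wards per hospital.
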